### Data collection and management

The assessors will collect data using a paper CRF. The research assistant will control the quality of data collection and input these data into Microsoft Excel. Double data entry will be employed to avoid data entry errors. The entered data will be imported into the data management platform FJTCM Yun, available at http://10.252.47.2, and managed by an independent agency. All data will be treated with the highest confidentiality. If a participant withdraws from the trial, the researchers will ask the participant if they would be willing to participate in the follow-up data collection. In that case, the researchers will make every effort to obtain follow-up data for the participant.

### Statistical analyses

#### Behavioural indicators of upper limb function level

Independent statisticians who will not participate in evaluations will analyse the data using SPSS Statistics for Windows Version 24.0, with *P* < 0.05 considered statistically significant. Continuous variables with a normal distribution will be presented as the mean ± standard deviation (SD), and continuous variables with a non-normal distribution will be presented as the median and interquartile range (IQR). Categorical variables will be reported as frequency or percentage. Basic data such as age, gender, and body mass index (BMI) will be considered covariates. The primary and secondary outcomes will be analysed according to the intention-to-treat (ITT) and protocol-compliant (PP) populations. The results of the ITT analysis will be compared with the results of the PP analysis to determine whether they are consistent. Multiple imputation will be used for missing data. ITT analysis will be performed on all Tai Chi and control group subjects. After the subjects are randomly divided into groups, they will be included in the assigned group for statistical analysis, even if they withdraw from the trial due to adverse reactions. Student’s *t* test or the Mann-Whitney *U* test will be used to analyse the differences between the Tai Chi and the control groups at each time point (including at the end of the 4-week intervention). A linear mixed model with limited maximum likelihood and group × time interaction analyses will be performed. Pearson or Spearman correlation analysis will be used for normally and non-normally distributed data, respectively.

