#### Inclusion criteria

To be eligible to participate in the study, each participant must meet the following criteria:Meet the diagnostic criteria of ‘stroke’ in the diagnostic essentials of various cerebrovascular diseases adopted at the Fourth National Cerebrovascular Disease Academic Conference in 1995 and confirmed by head computed tomography or magnetic resonance imaging;The first stroke occurred between 2 weeks and 6 months prior to commencing the study;Unilateral cortical lesion (left or right hemisphere) or subcortical lesion involving the motor pathway;The muscle strength of the upper limb of the affected side is ≥ 3 and muscle tone is ≤ 2 based on the Modified Ashworth Scale (MAS);Right-handedness before stroke;Age between 50 and 70 years;Blood pressure stable and below 160/100 mmHg;A Mini-Mental State Examination (MMSE) score of > 17 points for illiterate participants, > 20 points for participants with a primary school education, and > 24 points for participants with a middle school and above education;Brunnstrom stage ≥ IV in the affected upper limb;Standing balance ≥ level 2, the ability to stand independently for more than 5 min, and the ability to walk independently for more than 6 m;Willing to sign the informed consent form and understand, accept, and implement the rehabilitation guidance.

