### Outcome measurements

The variables of this trial include basic characteristics, primary and secondary outcomes, and exploratory results. The basic characteristics will be determined from a questionnaire administered at baseline (1–2 weeks before randomization). The primary and secondary outcomes will be measured at baseline and at the end of the intervention (4 weeks after randomization). The exploratory results will be measured at baseline and at the end of the intervention (4 weeks after randomization). All results will be assessed by experienced assessors who do not know the group assignments of the participants.

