#### Primary outcome measures

The primary outcome measure is the change in the FMA-UE scale score from baseline to the end of the 4-week intervention. The FMA-UE scale includes 33 items divided into four subscales (arm, wrist, hand, and coordination), each scored on a 3-point sequential scale [37]. Scoring is based on performing independent actions inside and outside the synergy pattern. The maximum score of 66 corresponds to undamaged motor function. The FMA-UE scale is often used to classify the severity of stroke injury, and the scale shows good reliability and validity. A FMA-UE score between 32 and 57 indicates moderate upper limb injury and an FMA-UE score between 58 and 65 indicates mild injury of the contralateral arm. FMA-UE sensation (0–12), passive range of motion, and pain (0–24) will also be assessed.

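### The primary outcome is change in FMA-UE, but the plan lists a score comparison at each visit beside a group × time mixed model, ranks neither, and does not name baseline FMA-UE as a covariate

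*Protocol article*

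**What the plan says.** Under Primary outcome measures: "The primary outcome measure is the change in the FMA-UE scale score from baseline to the end of the 4-week intervention". Outcome measurements gives two visits: "The primary and secondary outcomes will be measured at baseline and at the end of the intervention (4 weeks after randomization".

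The analysis is set out under Behavioural indicators of upper limb function level. A Student's t or Mann-Whitney U "test will be used to analyse the differences between the Tai Chi and the control groups at each time point". The same paragraph adds: "A linear mixed model with limited maximum likelihood and group × time interaction analyses will be performed". On populations: "The primary and secondary outcomes will be analysed according to the intention-to-treat (ITT) and protocol-compliant (PP) populations". On adjustment: "Basic data such as age, gender, and body mass index (BMI) will be considered covariates". A P value below 0.05 is "considered statistically significant".

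The paragraph does not say which test, or which population, decides the primary outcome. It does not say which of the analyses takes the covariates. Baseline FMA-UE is not among those named.

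**The concern.** Three things do not fit together.

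- **The per-visit test is not a test of the endpoint.** With two visits it yields a week-4 score comparison and a baseline comparison. The first is not a comparison of change. The second only asks whether randomisation produced a chance difference. By contrast, the article does write out a between-group t test of change for the exploratory connectivity values in its fNIRS, EEG and EMG analysis section.
- **Nothing is ranked.** Two analyses (the per-visit test and the mixed model) in two populations give four candidate primary results, before the choice between t and Mann-Whitney. ITT and PP are to be compared for consistency, but neither is said to be decisive.
- **Baseline FMA-UE is measured in everyone but not named as a covariate.** The t and Mann-Whitney tests cannot carry covariates at all, so on that route the baseline measurement is unused.

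At stake are precision in a trial of 84 participants, and whether a reader can tell which result was meant to decide the question.

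**Working it through.** **Inputs from the article.** Post-intervention scores 60.50 ± 2.19 and 59.14 ± 1.77; effect size 0.6830377; 5% type I error; 80% power; 64 evaluable; 20% dropout; 42 randomised per arm (Sample size estimation). The two visits are from Outcome measurements.

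**Assumptions.** Two-sided testing (sidedness is not stated for the behavioural outcomes). Correlation r between baseline and week-4 FMA-UE of 0.3, 0.5 or 0.7 (not given). Equal SD at both visits. Equal expected baseline means, so the treatment difference is the same on the score and change scales. Analysed number 42 × 0.8 = 33.6 per arm.

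**Step 1: the plan's own figures.** Pooled SD = √[(2.19² + 1.77²)/2] = 1.991. Then d = (60.50 − 59.14)/1.991 = 0.6830, which reproduces the stated effect size. It is a contrast of post-intervention scores, not of changes. The stated 64 does not reproduce with a two-sided t test: 32 per arm gives 76.7% power, and 35 per arm (70 in total) are needed for 80%. That is a separate matter; it is why the t test below sits just under 80%.

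**Step 2: what each analysis estimates.** With visits at baseline and week 4 only, the interaction in a mixed model that leaves the two baseline means free is (Tai Chi week 4 − Tai Chi baseline) − (control week 4 − control baseline). That is the between-group difference in change, so it matches the endpoint. The week-4 test compares scores and sets baseline aside. ANCOVA compares week-4 scores adjusted for baseline.

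**Step 3: precision.** Relative to the week-4 score contrast (variance 1), the variances are 2(1 − r) for change and 1 − r² for ANCOVA. The effective standardised effects are therefore:

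- week-4 t test: d
- unconstrained interaction: d/√[2(1 − r)]
- ANCOVA: d/√(1 − r²)

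**Step 4: power.** Non-central t, noncentrality = effective d × √(33.6/2). For the week-4 t test this is 0.683 × 4.099 = 2.80.

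| Assumed r | Week-4 t test | Unconstrained group × time | ANCOVA |
|---|---|---|---|
| 0.3 | 78.8% | 64.5% | 82.4% |
| 0.5 | 78.8% | 78.8% | 89.0% |
| 0.7 | 78.8% | 94.5% | 97.1% |

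ANCOVA gains 3.6, 10.2 and 18.3 points over the week-4 t test, and 17.9, 10.2 and 2.6 points over the unconstrained interaction. With all 42 per arm analysed the order is the same: 87.1% for the t test, and 90.0% (r = 0.3) to 99.1% (r = 0.7) for ANCOVA.

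**Step 5: cost of leaving the choice open.** Under the null, the week-4 and change contrasts correlate at √[(1 − r)/2], which is 0.59, 0.50 and 0.39 for r = 0.3, 0.5 and 0.7. The chance that at least one is significant at two-sided 5% is then 8.8%, 9.1% and 9.4% (bivariate normal). A simulation with 33 per arm and 20,000 runs gave 9.1% at r = 0.5 and 9.3% at r = 0.7.

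**The case against.** The strongest reply is that the plan already contains a sound analysis of its endpoint. The mixed model's interaction is the difference in change, and baseline FMA-UE enters that model as a repeated outcome, so its absence from the covariate list is not an error there. This stands. It means that the large gain at r = 0.7 (18 points) applies only to the t or Mann-Whitney route. Against the interaction the gain at that correlation is under 3 points, and if the model constrains the baseline means to be equal it is close to ANCOVA. The article does not say which form is meant.

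Other points on that side also stand:

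- Student's t or Mann-Whitney is one analysis with a switch, not two.
- The week-4 comparison is unbiased under randomisation and holds its 5% level. Ignoring baseline costs precision, not validity.
- The covariate sentence gives examples, so the list is open, and a statistical analysis plan may add baseline.
- The article does not say that the team will report whichever test is significant.

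What the reply does not answer is the ranking. The article is not silent here and does not simply defer detail: it states two analyses of the primary outcome that answer different questions, in two populations, and puts none first.

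**Conclusion.** The point holds in a limited form. The stated endpoint is change; one of the two listed analyses does not test it and ignores baseline, the other does test it, and nothing says which decides. Naming a baseline-adjusted analysis would improve on both listed routes at each correlation examined. At r = 0.5 the gain is about 10 points of power over either; at r = 0.3 it is mostly over the interaction, and at r = 0.7 mostly over the t test. These sizes rest on the assumed correlations, equal SDs, two-sided testing and 33.6 analysed per arm.

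Three stronger readings are not supported:

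- That the plan never tests its endpoint or never uses baseline. The interaction does both.
- That the trial's type I error is 9%. That figure arises only if success is claimed on either test, which the article does not propose.
- That leaving out time since stroke is an error. Eligibility spans a wide window ("The first stroke occurred between 2 weeks and 6 months prior to commencing the study"), but the article gives no data on how strongly this predicts week-4 FMA-UE.

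**What to change.** In the behavioural statistics section, name one primary analysis in the ITT population. Either of these would serve:

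- ANCOVA of week-4 FMA-UE on group, adjusted for baseline FMA-UE; or
- the planned restricted maximum likelihood mixed model, with a common baseline mean for the two groups stated explicitly.

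Report the adjusted group difference with its 95% confidence interval. State which covariates enter that model. Drop the significance test at baseline. Label the t or Mann-Whitney comparison, the change-score analysis and the PP analysis as supportive.

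Adjusting for time since stroke, or using a bootstrap interval in place of Mann-Whitney, is optional and not needed to resolve this point.

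The cost is wording only. Baseline FMA-UE is already measured and no new data are needed. The change should be recorded before any results by group are seen.

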### Sample size estimation

This trial will observe the effects of Tai Chi on upper limb function of post-stroke patients. When calculating the required sample size using the Gpower V.3.1.9.2 software, the Fugl-Meyer Assessment Upper Extremity (FMA-UE) scale served as the primary outcome measure. Based on a published study [33], the FMA-UE scores of stroke patients in the Tai Chi and control groups after intervention were 60.50±2.19 and 59.14±1.77 points, respectively. According to these results, a sample size of 64 participants would be sufficient to detect the target effect size (0.6830377) with a type 1 error of 5% (*α* = 0.05) and 80% power (*β* = 0.20). Assuming a dropout rate of 20%, a total of 84 participants are necessary, with 42 participants in each group.

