#### Tai Chi group

This group will receive Tai Chi training, routine medical care, health education, and rehabilitation training. The routine care, education, and rehabilitation training will be the same as described for the control group. The Tai Chi training will be led by Tai Chi coaches with more than 5 years of qualification. Tai Chi training follows a gradual process from part to whole and from easy to complex. The teacher will choose the appropriate form of Tai Chi according to each participant’s ability. When adjusting Tai Chi training for each participant, two fundamental principles are used: (1) the participant should be able to practice Tai Chi while relaxing and (2) there should be as much overall coordination as possible. The participant relaxes his/her muscles and joints as much as possible and focuses on movements that help him/her relax, completing these movements with minimal effort. The movement is slow, repetitive, and, if necessary, carried out in sections. Eight Tai Chi poses will be adopted in this study: Starting Posture, Parting the Wild Horse’s Mane on both sides, Brush Knee and Twist Step on both sides, Forearm Rollings on both sides, Grasp the Bird's Tail – Left Side, Grasp the Bird's Tail – Right Side, Cloud Hands, and Closing Form. These poses have been selected based on the literature [4, 36]. Please refer to 24 simplified standard movements of Tai Chi promoted by the General Administration of Sport (http://www.sport.gov.cn/). In the actual training process, the accuracy and consistency of the posture routine will not be emphasized. At the same time, according to the actual movement ability of the patient, the difficulty of reaching the posture standard will be appropriately reduced. The participants will receive five 60-min sessions per week, for a total of 20 sessions. Each session will include 5 min of warm-up, 50 min of Tai Chi training, and 5 min of cooldown. The training will be conducted at Fujian provincial rehabilitation hospital. The researchers involved in this trial will not carry out relevant concomitant care and interventions that are permitted or prohibited during the trial.

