We will use several methods to improve the quality of this trial. Senior physical education teachers will act as Tai Chi coaches to ensure the quality of the Tai Chi training. The participants in the Tai Chi group will gather at a fixed time and place to practice. To control deviation caused by the amount of exercise, all participants will be required to keep an activity log. In addition, Tai Chi training will be supervised by two research assistants to ensure that both coaches and participants practice carefully. However, this trial may have some potential limitations. First, it is difficult for people involved in non-drug randomized controlled trials to be blind to the treatment. Indeed, in this study neither the coaches nor the participants can be blind to the treatment. Tai Chi coaches cannot participate in this study’s recruitment, evaluation results, or data analysis, and performance differences may be inevitable. Second, there is no follow-up. Finally, all participants will come from the same city, reducing the sample’s representativeness.

Tai Chi emphasizes the ‘unity of form and spirit’. When the ‘movement intention’ is generated, the corresponding brain regions are excited, and the resulting nerve impulses excite the muscle groups, thus completing the ‘voluntary movement’. This is the process of ‘the mind following the movement’ [43]. Through Tai Chi exercise, we can regulate the body, mind, and collaterals to promote recovery of upper limb function in post-stroke patients. This project will focus on the connection between the neural network (sensorimotor frontoparietal network) and the muscle network; consider the brain plasticity theory; and employ advanced research techniques such as fNIRS, EEG, and EMG to investigate the mechanism by which Tai Chi promotes functional recovery of upper limbs after stroke. This trial will advance the field, as the available research on the effect of Tai Chi on upper limb function after stroke has mainly focused on the overall effect on upper limb function and nerve excitability. These studies have not reported the mechanism for the interaction between the sensorimotor frontal-parietal cortex network and upper limb muscle activation mode of upper limb function.

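### Shared coaches in the Tai Chi arm only are not allowed for in the sample size or in the listed between-group tests; a cheap sensitivity analysis would show whether this matters

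*Protocol article*

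**What the plan says.** All references are to the Protocol article.

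- **Randomization and allocation concealment:** individuals are allocated 1:1.
- **Tai Chi group:** training is led by coaches, in the plural. On their discretion: "The teacher will choose the appropriate form of Tai Chi according to each participant’s ability". Posture difficulty is also eased to suit ability.
- **Discussion:** "The participants in the Tai Chi group will gather at a fixed time and place to practice".
- **Study design and Control group:** controls have no Tai Chi. Occupational therapists treat participants in both arms.
- **Sample size estimation:** the reference scores "were 60.50±2.19 and 59.14±1.77 points, respectively"; from these the article concludes that "a sample size of 64 participants would be sufficient", and 84 are recruited to cover 20% dropout. No design effect appears.
- **Behavioural indicators of upper limb function level:** Student's t or Mann-Whitney "test will be used to analyse the differences between the Tai Chi and the control groups at each time point". A linear mixed model fitted by restricted maximum likelihood with a group by time interaction is listed next to it. Neither is named as the primary analysis, and the model's random effects are not described.

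**The concern.** This is a partially nested design. Participants in one arm share coaches, and perhaps sessions; those in the other arm do not. The coaches have real discretion, so results could differ from coach to coach. A t or Mann-Whitney test on individual scores cannot carry such a component: it takes every participant as a separate piece of information.

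If a coach or class component exists, the interval for the Fugl-Meyer difference is too narrow and the nominal 5% is exceeded. The same holds for the other behavioural outcomes analysed this way. With few coaches, the effect of Tai Chi also cannot be separated from the effect of these particular teachers. That matters because the abstract says positive results will verify that Tai Chi works, and the Discussion argues for wider use.

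**Working it through.** **1. The plan's own figure.** The difference is 60.50 − 59.14 = 1.36. The pooled SD is √[(2.19² + 1.77²)/2] = 1.991. The effect size is 1.36/1.991 = 0.683, as stated. Sidedness is not stated, so two-sided 5% is assumed. For two independent samples the non-centrality is 0.683 × √(n/2). The non-central t then gives:

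- 32 per arm (64): 76.7% power
- 34 per arm (84 × 0.8 = 67.2, about 34 each): 79%
- 35 per arm (70): 80.4%
- 42 per arm (84): 87%

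The effect size reproduces. Power of 80% at 64 does not, and this shortfall is there with no clustering at all. The calculation contains no intraclass correlation.

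**2. Inputs the document does not give (assumptions).** Intraclass correlation ρ of 0.01 to 0.10; k equal clusters of m = 42/k in the Tai Chi arm; independent controls; equal total variance in both arms.

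**3. True error of the listed t test.** The true variance of the difference is σ²[(1 + (m − 1)ρ)/42 + 1/42]. The test in effect uses 2σ²/42. The ratio is V = 1 + (m − 1)ρ/2. The true two-sided error is about 2 × P(T > 1.989/√V) on 82 degrees of freedom. Example with 3 coaches and ρ = 0.05: V = 1 + 13 × 0.05/2 = 1.325, √V = 1.151, 1.989/1.151 = 1.728, error 8.8%.

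| Clusters × size | ρ = 0.01 | ρ = 0.05 | ρ = 0.10 |
|---|---|---|---|
| 21 × 2 | 5.1% | 5.3% | 5.6% |
| 7 × 6 | 5.3% | 6.4% | 7.9% |
| 4 × 10.5 | 5.5% | 7.7% | 10.5% |
| 3 × 14 | 5.7% | 8.8% | 12.5% |
| 2 × 21 | 6.1% | 10.8% | 16.3% |

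Simulation at ρ = 0.05 agrees with these values to within about 0.2 percentage points. The standard error is understated by 1 − 1/√V. At ρ = 0.05 that is about 1% with clusters of 2, 6% with 7 clusters, 13% with 3 and 18% with 2.

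**4. Power of a test that respects the clustering.** With 34 per arm and ρ = 0.05, the variance is (1 + (m − 1)ρ)/34 + 1/34 in SD² units, with Satterthwaite degrees of freedom. Power is 78% with 17 clusters of 2, 72% with 7 clusters, 63% with 4 and 54% with 3, against 79% for independent data. The last two rest on only about 8.5 and 5.4 degrees of freedom, too few for the coach variance to be estimated well.

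**5. What the timeline suggests about class size.** The Trial status section gives a start in mid-March 2022 and a target of December 2024, about 146 weeks. Tai Chi takes 42 × 4 = 168 participant-weeks, so on average 168/146 = 1.2 participants train at once. If enrolment were squeezed into one year (an assumption), it is 168/52 = 3.2.

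**The case against.** **Large classes are not documented and look unlikely.** A fixed time and place does not mean that all 42 train together. Participants are randomised singly and assessed 4 weeks later, which leaves little room to assemble cohorts, and step 5 points to one to three training at once. This stands. Class clustering may well be negligible, and what remains is mainly coaches shared over time.

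**No participant is tied to one coach.** If coaches rotate across the 20 sessions, any shared effect belongs to the whole arm and no random effect can recover it. Tailoring to the individual may also lower the correlation. Both points stand: they limit what a model can do, but not the value of recording who taught whom.

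**The article may leave random effects to a fuller plan.** This stands for the mixed model. A reader might infer that it treats participants as independent, but the text only fails to name a coach or class term. It does not stand for the t and Mann-Whitney tests, which are named and cannot carry such a term.

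**The largest error rates come from two to four coaches**, where a random-effects model is hardly usable. That is fair, and the fix has a separate route for that case. It does not make the listed tests valid there.

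**Conclusion.** The concern holds in a conditional form. The sample size and the listed t and Mann-Whitney tests take participants as independent although one arm shares coaches. With a positive coach or class correlation, two-sided error exceeds 5%. Over the range shown it runs from 5.1% to 16.3%; at ρ = 0.05 it is 6.4% with 7 clusters and about 11% with 2 coaches. The correlation, coach count and class size are all assumed, and with clusters of 2 or 3 there is little to correct.

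Three stronger readings are not supported:

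- A reader might infer that the stated 80% power holds only without clustering. In fact 64 participants give 76.7% even then, while all 84 give 87%, and about 86% at ρ = 0.01 with 14 per coach.
- A reader might infer that the t test is the primary analysis. It is listed beside the mixed model without ranking.
- A reader might infer that the results are tilted towards Tai Chi. Ignored clustering makes false findings more frequent in both directions.

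This is a worthwhile, inexpensive improvement. It is not evidence that the planned result will be wrong.

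**What to change.** 1. Record on the CRF the coach or coaches, and the training cohort if sessions are shared, for every Tai Chi participant. Fill this in from training records for those already treated.
2. In the statistical analyses section, add a sensitivity analysis that extends the planned restricted maximum likelihood model with a coach or class random effect on the change from baseline in the Tai Chi arm only. Each control is their own cluster, and Satterthwaite degrees of freedom are used. Report its estimate and interval beside the independent-data result.
3. If there are too few coaches to estimate a variance (about 4 or fewer), or coaches rotate across participants, report the Fugl-Meyer change descriptively by coach where possible, and limit the conclusion to Tai Chi as taught by these coaches.
4. In the sample size section, state that the power calculation assumes no clustering by coach or class.

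The cost is one CRF field, one extra term in a model already planned and a sentence in each of two sections. No patients or procedures are added. The downside is a wider interval in the sensitivity analysis, most of all when coaches are few.

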**Discussion:**

This randomized controlled trial will examine the effectiveness of Tai Chi in stroke patients with upper limb dysfunction and explore the neurophysiological mechanism. Positive results will verify that Tai Chi can improve upper limb function of stroke patients.

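### The primary outcome, FMA-UE change, is analysed by two unranked tests, one of which does not test change; a single baseline-adjusted ITT analysis should be named as primary

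*Protocol article*

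**What the plan says.** Under Primary outcome measures: "The primary outcome measure is the change in the FMA-UE scale score from baseline to the end of the 4-week intervention". Under Outcome measurements: "The primary and secondary outcomes will be measured at baseline and at the end of the intervention (4 weeks after randomization"), so there are two time points and no others.

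Under Behavioural indicators of upper limb function level, two between-group analyses are prescribed. The first is a two-sample test, either Student's t or Mann-Whitney U, which "will be used to analyse the differences between the Tai Chi and the control groups at each time point", with the end of the 4-week intervention given as one of those points. Then: "A linear mixed model with limited maximum likelihood and group × time interaction analyses will be performed". One threshold, P < 0.05, is "considered statistically significant" throughout. The same paragraph says "Basic data such as age, gender, and body mass index (BMI) will be considered covariates", and has primary and secondary outcomes analysed in both the ITT and PP sets, with the two sets compared for consistency.

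Sample size estimation sizes the trial on post-intervention scores (60.50 ± 2.19 against 59.14 ± 1.77), with 5% type 1 error and 80% power.

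**The concern.** A change score does not exist at baseline, so a test at each time point can only be a test of the score at that point. For the primary outcome this has three consequences. The t or U test does not address change. It leaves the recorded baseline FMA-UE out of the week-4 comparison. It also includes a significance test at baseline, where any difference between randomised arms is due to chance. The interaction does address change, but the article does not say that it is the deciding analysis, and the sample size was built on the other quantity.

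The trial's main question can therefore receive two different answers, with no stated rule for when they conflict. The abstract says "Positive results will verify that Tai Chi can improve upper limb function of stroke patients", so what counts as positive matters. The stated 5% error is secure only if one test is fixed in advance. Blinded A/B group labels do not remove the choice, because both P values are visible under the labels.

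**Working it through.** **Inputs from the article.** Means and SDs as above; 42 per group; 20% dropout, so 42 × 0.8 = 33.6, taken as 34 per arm; α = 0.05, taken as two-sided because sidedness is not stated.

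**Assumptions.** Normal data, complete pairs, equal SDs at both times. The baseline/week-4 correlation ρ is not in the article and is varied from 0.3 to 0.9.

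**Planned effect.** d = (60.50 − 59.14)/√((2.19² + 1.77²)/2) = 1.36/1.991 = 0.683, which reproduces the stated 0.6830377. (The stated 64 participants do not reproduce; that is a separate matter and does not enter here.)

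**How far the two tests overlap.** With both SDs set to 1, let B be baseline and P the week-4 score.
- The week-4 test uses P. With complete data and two times, the interaction uses P − B.
- Cov(P, P − B) = 1 − ρ and SD(P − B) = √(2(1 − ρ)).
- The correlation of the two test statistics is r = (1 − ρ)/√(2(1 − ρ)) = √((1 − ρ)/2).

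**Risk that at least one rejects when there is no effect.** This is 1 − Pr(|Z₁| < 1.96 and |Z₂| < 1.96), with Z₁ and Z₂ bivariate normal with correlation r. The value for independent tests is 1 − 0.95² = 9.75%. If the mixed model instead forces a common baseline mean, it behaves like a baseline-adjusted analysis and r = √(1 − ρ²).

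| ρ | r | Either rejects, calculated | Either rejects, simulated (42 per arm, 40,000 runs) | Either rejects, common-baseline model |
|---|---|---|---|---|
| 0.3 | 0.592 | 8.8% | 8.7% | 6.4% |
| 0.5 | 0.500 | 9.1% | 8.9% | 7.3% |
| 0.7 | 0.387 | 9.4% | 9.2% | 8.3% |
| 0.9 | 0.224 | 9.6% | 9.5% | 9.2% |

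In the same simulations each test alone rejected in 4.7 to 5.1% of trials. Using the U test in place of the t test gave 8.7, 8.8, 9.2 and 9.5%. If the week-4 SD is 0.7 or 1.3 times the baseline SD (ρ 0.5 to 0.9), the calculated risk is 8.4 to 9.75%.

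**Power at the planned effect, 34 per arm.** The noncentrality of the week-4 t test is d√(n/2) = 0.683 × √17 = 2.82. For the interaction it is 2.82/√(2(1 − ρ)); for the baseline-adjusted analysis it is 2.82/√(1 − ρ²).
- ρ = 0.5: 2.82, 2.82 and 3.25. Simulated power 79%, 79% and 89%.
- ρ = 0.7: 2.82, 3.64 and 3.94. Simulated power 79%, 95% and 97%.

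Since 1 − ρ² ≤ 1 and 1 − ρ² = (1 − ρ)(1 + ρ) ≤ 2(1 − ρ), the adjusted analysis is at least as precise as either planned test at every ρ, apart from the degree of freedom spent on baseline. At ρ = 0.5 the two planned tests tie; the week-4 test is the weaker of them only above 0.5.

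**Disagreement at the planned effect.** Over ρ from 0.3 to 0.9, one test is significant and the other is not in about 20 to 27% of simulated trials with 34 per arm, and about 13 to 22% with 42 per arm.

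**The case against.** The strongest reply is that the harm is conditional. Nothing in the article says that success is declared if either test is significant, and each test alone holds 5%. A reader might infer that the trial as planned runs at a 9% error rate. The article does not support that: the abstract's remark about positive results is discussion prose, not a decision rule. This part of the objection stands, and the 9% has to stay conditional.

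It can also be said that the definition of the outcome already points to the interaction, since with two time points that is the difference in mean change, and that the by-time-point tests are accompanying descriptions. This is a fair reading, but the article does not state it, and the sample size rests on the other comparison.

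A third reply is that ranking analyses is commonly left to an analysis plan, which is not shown. Silence on ranking would indeed be no finding. What remains is in the text itself: a prescribed test that does not match the stated primary outcome, next to one that does, at the same threshold.

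Two further points might be added to the charge but carry little weight. The covariates cannot enter a t or U test, but they can enter the mixed model, so there is no contradiction. The ITT and PP sets are compared for consistency, which is a sensitivity role and not a second chance at success. The baseline test is uninformative but cannot produce an efficacy claim, and it is not part of the 9%.

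Finally, group means near 60 on a scale with maximum 66 make normality doubtful, so the figures are indicative.

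**Conclusion.** The point holds in a limited form. The primary outcome is given two unranked between-group tests at P < 0.05, and the one at each time point tests the score, not change. If either were allowed to decide, the false-positive risk would be about 8.8 to 9.6%, or about 6.4 to 9.2% if the mixed model constrains baseline means to be equal, which the article does not describe. The chance of conflicting answers at the planned effect is roughly 20 to 27% with 34 per arm. These figures rest on normal data, complete pairs, equal SDs and an assumed correlation of 0.3 to 0.9. The group × time model is itself a valid analysis of change; the faults are the missing choice and the mismatch of the other test. This should be fixed, but it does not invalidate the design.

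**What to change.** Name one primary analysis in the ITT set: week-4 FMA-UE in a linear model with arm, baseline FMA-UE and the named covariates, or the equivalent mixed model with a common baseline mean. Report the adjusted mean difference with its 95% confidence interval. The primary outcome need not be redefined: once baseline is in the model, the arm coefficient is the same whether week-4 score or change is the response. State that the by-time-point tests, the unconstrained interaction and the PP set are supportive, and drop the significance test at baseline.

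This holds the error at 5% and uses only data already planned. The cost is a change of wording in the analysis section, which must be made before database lock.
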